#### Procedure for unblinding if needed {17b}

There is no need of unblinding.

### Data collection and management

#### Plans for assessment and collection of outcomes {18a}

The primary outcome is change in CRF measured with the validated CFS-D questionnaire [30]. The secondary outcomes are sleep quality, measured with the Pittsburgh Sleep Quality Index (PSQI) [31], and patient’s HRQL, measured with the European Organization for Research and Treatment of Cancer Questionnaire C30 (EORTC-QLQ-C30) [32].

After obtaining written informed consent and inclusion in this study, sociodemographic and clinical data are surveyed, and questionnaires will be given to participants. All questionnaires will be collected prior to and post-treatment and during follow-up 6, 12, and 24 months after the start of the tango module (Fig. 1).

#### Plans to promote participant retention and complete follow-up {18b}

If there are problems with participation in a tango session, a phone call will be made to find ways to continue attendance. For the follow-up surveys, participants will be contacted by postal mail, by stamped return envelopes enclosed, and by personal telephone calls.

#### Data management {19}

Pseudonymized data will be collected with paper case report forms and paper-based questionnaires. All essential trial documentation will be kept within the Trial Master File. For all collected data, pseudonymized data entry is performed at the study center by members of the research staff [36, 37]. Clinical and demographic data will be retrieved from the patients during the informed consent interview by the study physician.

#### Confidentiality {27}

Data management and processing of the pseudonymized collected data are subject to the General Data Protection Regulation (GDPR). In order to protect the confidentiality, the pseudonymized collected data will be stored for 15 years after the end of this study in a pseudonymized form at the study center of the FIH at the GKHB. The pseudonymized data may only be reviewed by authorized persons of the research team. No third parties will have access to these data.

#### Plans for collection, laboratory evaluation, and storage of biological specimens for genetic or molecular analysis in this trial/future use {33}

No biological specimens will be collected.

## Statistical methods

### Statistical methods for primary and secondary outcomes {20a}

All statistical analyses will be performed using Excel 2010 (Microsoft, USA) and the software R (R version 4.0.5) [38]. Baseline data will be summarized using descriptive statistics. Continuous variables will be described as means with standard deviation and median with interquartile range (IQR), categorical variables will be summarized as frequencies and percentages. Student’s *t*-tests will be applied, and *p*-values < 0.05 are considered to be significant. For the characterization of group differences, Pearson’s chi-squared tests with Yates’ continuity correction and Student’s *t*-tests will be performed. The detection of longitudinal effects will be characterized with Student’s *t*-tests and to identify influencing factors and to address potential sources of bias and potential confounders, and adjusted multivariable linear regression analyses will be performed. In order to yield reliable model results, stepwise regression selections will be performed, and models with high adjusted *R*^2^ will be chosen. According to Cohen’s interpretation [39], *R*^2^ values between 13 and 25% indicate medium, and *R*^2^ values 26% or above indicate high effect sizes. In addition to statistical significance, we will report descriptive statistics and effect size estimates.

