**Methods:**

Sixty patients with a diagnosis for stage I–III breast cancer 12–48 months before enrollment and with CRF (age > 18) will be recruited and randomized 1:1 to a tango or a waiting-list group. Movement concepts using elements of Argentine tango (self-awareness, musical and spatial perception, self-perception, playfulness, shared experience) will be examined with the participants during six consecutive weekly 1-h tango sessions. The primary outcome will be the improvement of CRF (German version of the Cancer Fatigue Scale), and the secondary outcomes will be the improvement in sleep quality (Pittsburgh Sleep Quality Index) and quality of life (EORTC-QLQ-C30). Patient-reported outcomes will be measured at baseline and 6 weeks later; follow-up will be performed 6, 12, and 24 months after baseline. An evaluation will be performed by means of descriptive data analyses.

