
### Objectives {7}

This study protocol describes a randomized controlled trial for patients with breast cancer and increased CRF receiving either Argentine tango in a tango group or no Argentine tango in a waiting-list control group. The primary outcome measure is the change of CRF levels after 6 weeks. (A) The CRF changes of patients of the tango group will be compared to the waiting-list control group, and (B) prior to and post the 6-week Argentine tango treatment, the CRF changes are evaluated for the whole study cohort. The primary hypothesis is that a module consisting of six consecutive weekly 1-h Argentine tango lessons will promote a significant reduction of fatigue symptoms. Secondary objectives are the improvement of self-reported sleep quality and HRQL, prior to and post the Argentine tango treatment, and to explore the effects after 6, 12, and 24 months follow-up.

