### Methods for additional analyses (e.g., subgroup analyses) {20b}

Subgroup analyses will be performed regarding the possible confounders such as concurrent endocrine treatment, concomitant medications for symptom relief, and sport activity. Multilevel modeling can be used for subgroup analyses and to account for confounding variables. Confounding variables (age, body mass index, tumor stage, hormonal status, endocrine treatment, concomitant medication, sport activity, and the respective outcome values at baseline) will be considered. Furthermore, adjusted multivariable linear regression analyses will be performed, to address potential confounders and influencing factors.

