### Methods in analysis to handle protocol non-adherence and any statistical methods to handle missing data {20c}

Patients who are unable to participate in the tango treatment or withdraw consent to participate in the study will be excluded and not replaced. If individual sessions cannot be attended, this will be noted, and the surveys will continue as planned. Regarding the evaluation of the questionnaires, we follow the EORTC-QLQ-C30 scoring manual on the calculation and handling of missing data. We do not plan to use imputation when reporting outcome data.

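### Follow-up change at 6, 12 and 24 months is to be judged by t-tests on returned pairs of forms, which can mistake selective return for lasting improvement; one mixed model per scale would use all recorded scores

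*Protocol article*

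**What the plan says.** The primary question is the change in fatigue at 6 weeks. Among the secondary objectives is "to explore the effects after 6, 12, and 24 months follow-up" (Objectives {7}). The abstract states that "follow-up will be performed 6, 12, and 24 months after baseline", and follow-up forms go out by post with prepaid envelopes and phone reminders.

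For change over time, Statistical methods {20a} states: "The detection of longitudinal effects will be characterized with" Student's t-tests. The general threshold is that p-"values < 0.05 are considered to be significant", with no adjustment and no exemption for follow-up. For influencing factors and confounders the same section adds that "adjusted multivariable linear regression analyses will be performed", with stepwise selection; this is not described as a repeated-measures model.

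On missing data, section {20c} says "We do not plan to use imputation when reporting outcome data". Patients who cannot take part in the tango treatment or who withdraw consent "will be excluded and not replaced". The reference to the EORTC scoring manual concerns the scoring of questionnaires and does not supply a method for forms never returned. Section {20b} says "Multilevel modeling can be used for subgroup analyses and to account for confounding variables", which is optional and serves another purpose than change over time.

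**The concern.** A t-test compares two means. With no imputation, a test of change from baseline to a given follow-up time can use only participants who returned both forms. That set differs between times and probably shrinks. A participant who reported no improvement at 6 weeks and 6 months and then stopped replying contributes nothing to the 24-month result, although her earlier scores are informative about it.

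The design makes this matter. Under the explanation of comparators {6b}, the waiting group receives the same tango module during follow-up, so there is no untreated arm at 6 to 24 months. The Discussion plans to learn from the entire cohort how lasting the effects are. That answer rests on within-person change, and no untreated comparison exists in which selective return could cancel. If those who benefit less stop replying, the tests will show persistence that did not occur.

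**Working it through.** **The plan's own figures.** The article gives no sample size, return rate or error rate for follow-up. Its only sample size, 25 per group, is for d = 0.8, 80% power and two-sided 5%. It reproduces by the normal approximation: 2 × (1.96 + 0.84)² / 0.8² = 24.5, rounded up to 25. The only loss figure is 20% dropout, not tied to 24 months.

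**Assumptions for the bias.** These are not from the article: 60 participants, SD 8 points on the 0-60 fatigue scale, true change zero at all times, five assessments (baseline, 6 weeks, 6, 12 and 24 months). Correlation is either equal (0.6) or first-order autoregressive (0.8 between successive visits). The log-odds of returning the 24-month form fall by b per SD of less improvement recorded so far, with b = 0.5 to 1.0, so the odds ratio is exp(-0.5) = 0.61 to exp(-1.0) = 0.37.

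**Simulated result of the paired t-test at 24 months** (negative = apparent improvement; ranges cover both correlation patterns and both odds ratios):

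| Return at 24 months | Spurious change (points) | False-positive rate of a nominal 5% test |
|---|---|---|
| 90% | -0.2 to -0.7 | about 6-9% |
| 80% | -0.4 to -1.2 | about 7-16% |
| 68% | -0.5 to -1.9 | about 7-30% |

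A likelihood-based estimate using all earlier scores is about 0 throughout.

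**Hand check of one cell.** Take 80% return and the autoregressive pattern. The number of pairs is 60 × 0.8 = 48. The baseline-to-24-month correlation is 0.8⁴ = 0.41, so the SD of change is 8 × √(2 × 0.59) = 8.7 and the standard error is 8.7 / √48 = 1.25. A bias of 1.2 is 1.2 / 1.25 = 0.96 standard errors. The rejection rate is P(Z > 1.96 - 0.96) + P(Z < -1.96 - 0.96) = 0.159 + 0.002 = 16%, as tabulated.

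**Scale.** At SD 8 the planned effect of d = 0.8 is 0.8 × 8 = 6.4 points. The 80% row is therefore 0.4 / 6.4 = 6% to 1.2 / 6.4 = 19% of it.

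**Where the bias vanishes.** If return depends only on the absolute 12-month score and correlations are equal, the paired change has a bias of about 0.

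**Where the model does not help.** If return depends on the unseen 24-month score (equal correlation 0.6, 60-80% return), the paired test is biased by -0.04 to -0.13 SD and the model by -0.05 to -0.18 SD. At SD 8 that is about -0.3 to -1.0 and -0.4 to -1.4 points.

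**Multiplicity.** Three follow-up times at 0.05 give 1 - 0.95³ = 14.3% if independent. Simulated paired tests sharing one baseline (48 pairs, equal correlation 0.3 to 0.7) give 12.5-12.8% per scale. Testing each at 0.05/3 gives 4.4-4.7%.

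**The case against.** The strongest reply is that the follow-up is exploratory. Objectives {7} says so, the abstract speaks of descriptive analyses, and effect sizes are promised beside p-values. This stands against making much of multiplicity. It does not excuse a biased estimate, and the 0.05 rule in {20a} is stated without exempting follow-up.

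A second reply is that bias is possible but not shown. No return rate is given, and envelopes and reminder calls may keep return high. This also stands, and is why the size is given over a range of return rates. A reader might infer from the 68% row alone that false positives of up to 30% are to be expected; the article does not support that, since its only loss figure is 20%.

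A reader might also count four tests per scale and quote 15.6-15.9%. That count includes the 6-week assessment, which is the separately specified primary time point. The follow-up times number three.

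It is tempting, too, to present a mixed model as removing the bias. It does so only when non-return depends on scores already recorded.

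Finally, a condensed article may leave model details to a fuller plan. But the article does not stay silent: it names the t-test for change over time and assigns multilevel modelling elsewhere. That the tests are separate and use returned pairs is an inference from these statements, and nothing in the article contradicts it.

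**Conclusion.** The point holds for the exploratory 6-, 12- and 24-month changes and does not touch the 6-week between-arm comparison. As planned, follow-up change rests on returned pairs and discards the earlier scores of non-returners. Whether this biases the result depends on why forms are missing, which the plan cannot know in advance. Under the stated assumptions the error is small at 90% return and reaches one to two points in the less favourable settings at 80% and 68%. The unadjusted 12.5% chance of at least one false positive per scale is secondary. The change is worth making because it is cheap and uses data already collected, not because the follow-up results are known to be wrong.

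**What to change.** In Statistical methods {20a}, replace the follow-up t-tests by one linear mixed model per scale:

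- Fit it by likelihood to all returned questionnaires from all randomised participants. No imputation is needed, so the preference in {20c} is kept; the exclusion of non-participants there should not apply to questionnaires already returned.
- Treat baseline as one of the outcome times and not also as a covariate. With baseline only as a covariate, a test of time would compare later visits with each other and not with baseline.
- Include categorical time, arm and arm-by-time, with an unstructured or subject-level covariance.
- Define follow-up time from one origin. The abstract counts from baseline, Outcomes {12} from completion of the module, and {18a} from its start; these differ, and differ by arm.
- Report change from baseline at each time with a 95% confidence interval, described as exploratory within-cohort change. Arm differences at later times are not tango versus control, because the waiting group receives the module.
- State that the model removes bias only when non-return depends on recorded scores, and add a simple sensitivity analysis for dependence on unseen scores.
- Keep the 6-week between-arm contrast as the primary test.

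The cost is a little more analysis work in R, which the article already names, and a less familiar presentation than t-tests. No new data are needed.

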### Interim analyses {21b}

No interim analysis will be performed. No unblinded interim results have been and will not be presented anywhere.

### Methods for additional analyses (e.g., subgroup analyses) {20b}

Subgroup analyses will be performed regarding the possible confounders such as concurrent endocrine treatment, concomitant medications for symptom relief, and sport activity. Multilevel modeling can be used for subgroup analyses and to account for confounding variables. Confounding variables (age, body mass index, tumor stage, hormonal status, endocrine treatment, concomitant medication, sport activity, and the respective outcome values at baseline) will be considered. Furthermore, adjusted multivariable linear regression analyses will be performed, to address potential confounders and influencing factors.

### Methods in analysis to handle protocol non-adherence and any statistical methods to handle missing data {20c}

Patients who are unable to participate in the tango treatment or withdraw consent to participate in the study will be excluded and not replaced. If individual sessions cannot be attended, this will be noted, and the surveys will continue as planned. Regarding the evaluation of the questionnaires, we follow the EORTC-QLQ-C30 scoring manual on the calculation and handling of missing data. We do not plan to use imputation when reporting outcome data.

### Plans to give access to the full protocol, participant level-data, and statistical code {31c}

The trial protocol and anonymized data on the group level may be shared with scientists who have medically or scientifically well-founded reasons; data protection according to GDPR and ethics according to ethical approval must be ensured.

### Oversight and monitoring

#### Composition of the coordinating center and trial steering committee {5d}

The trial coordination team meets regularly with the chief investigator, study physicians, tango teacher, and further research team members. The study design, study protocol, data management, and all study-related documents are critically reviewed. The coordinating investigator is responsible for the trial registration, revisions of the study protocol and application/amendments to the ethics committee, and scheduling of regular team meetings. All involved investigators and team members ensure compliance with the study protocol and ensure the follow-up according to the protocol. The steering committee consisting of clinical experts and sponsor’s staff is not directly involved in the study and ensure the scientific quality of the study, the study protocol, and the study report.

#### Composition of the data monitoring committee, its role, and reporting structure {21a}

Not applicable, this trial is not monitored.

#### Adverse event reporting and harms {22}

During each tango session, information on the occurrence of adverse events is regularly retrieved and documented. Adverse events related to the tango treatment during the 6-week sessions will be recorded by the coordinating investigator.

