### Eligibility criteria {10}

#### Inclusion, exclusion, and dropout criteria for participants

Participants will be eligible to join the study if they had been diagnosed with breast cancer, have increased levels of fatigue, are willing to participate in this study, and if they meet all following criteria:
Signed written informed consentAge ≥ 18 yearsStage I–III breast cancer has been diagnosed 12–48 months before enrollmentIncreased levels of fatigue (≥ 12 points in the CFS-D questionnaire)Eastern Cooperative Oncology Group (ECOG) performance status 0–2

Patients will not be eligible for the study if they meet one or more of the following exclusion criteria:
No fatigue at all (≤ 12 points in the CFS-D questionnaire)Pregnancy or breastfeedingOccurrence of recurrences or metastasesConcurrent participation in other clinical trialsLinguistic, medical, psychiatric, cognitive, or other conditions that may compromise the patient’s ability to understand the patient information, comply with the study protocol, or complete the study

Participants must attend at least four of the six tango sessions and answer the questionnaires; if they do not, they will be considered dropouts.

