### Interventions

#### Explanation for the choice of comparators {6b}

The comparator is a waiting-list control group. All participants will be randomized to either the tango group or the waiting group. The participants of the waiting group will continue routine activities during the 6-week waiting period. During follow-up, patients from the waiting-list control group will receive the same Argentine tango module as the participants of the tango group. The follow-up assessments for both trial arms will be the same (Fig. 1).

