#### Criteria for discontinuing or modifying allocated interventions {11b}

Participants are encouraged to report any discomfort and to perform only movements that do not cause them any problems. If a participant does not attend a session, she is contacted by phone and asked how she is feeling, and options are sought to continue her tango sessions. Adapting to the current COVID-19 pandemic conditions, the tango sessions are conducted in compliance with the national security and hygienic regulations, i.e., all dance movements, including paired actions, will be performed at a distance of 2 m to each other, the tango sessions will be conducted in a large therapy room with adequate oxygen ventilation, and the patients as well as the teacher are wearing surgical masks during the session. Before entering the therapy room, the teacher and the patients have to disinfect their hands with adequate disinfection detergent (including > 75% ethanol). Protective policies are constantly adapted to the locally applicable regulations; currently, participants must be vaccinated or have a valid negative SARS-CoV2 test to participate in Tango sessions.

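### Adverse events are systematically asked about only at tango sessions, so harms have no concurrent comparator, and the text is unclear on whether unrelated events are kept

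*Protocol article*

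**What the plan says.** The harms section of the protocol article, Adverse event reporting and harms {22}, has two sentences. The first sets when events are sought: "During each tango session, information on the occurrence of adverse events is regularly retrieved and documented". The second sets what is recorded, by whom and over what period: "Adverse events related to the tango treatment during the 6-week sessions will be recorded by the coordinating investigator".

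On the comparator, Explanation for the choice of comparators {6b} says: "The participants of the waiting group will continue routine activities during the 6-week waiting period". It then adds: "During follow-up, patients from the waiting-list control group will receive the same Argentine tango module as the participants of the tango group".

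Criteria for discontinuing or modifying allocated interventions {11b} gives two further routes by which a problem could come to light. One is spontaneous: "Participants are encouraged to report any discomfort and to perform only movements that do not cause them any problems". The other is a telephone contact: "If a participant does not attend a session, she is contacted by phone and asked how she is feeling". Neither is described as feeding the adverse-event record.

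Participants who do not complete the module are covered in two places. The dropout rule in the eligibility section reads: "Participants must attend at least four of the six tango sessions and answer the questionnaires; if they do not, they will be considered dropouts". The section on non-adherence and missing data {20c} adds: "Patients who are unable to participate in the tango treatment or withdraw consent to participate in the study will be excluded and not replaced".

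**The concern.** In a randomised trial the control arm can show which events would have happened anyway. These participants have fatigue and are 12 to 48 months past a breast cancer diagnosis, so symptoms unrelated to tango can be expected in both arms. If adverse events are sought in one arm only, a case-by-case judgement of relatedness has to do the work that a comparison of arms would do better.

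Two smaller problems sit alongside this. If relatedness is a condition for entering the record, it cannot be re-examined later, because the events judged unrelated are not there. And if enquiry happens at sessions, someone who stops coming is no longer asked in the stated way, whatever her reason for stopping.

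At stake is the harms report of this trial. The fatigue comparison is not affected.

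**Working it through.** The plan gives no figure to reproduce here. The check sets the sections side by side and counts the stated occasions on which an adverse event would be asked about during the randomised 6 weeks.

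| Contact in the randomised 6 weeks | Tango group | Waiting group | Stated as adverse-event collection? |
|---|---|---|---|
| Enquiry at each session ({22}; six weekly sessions, {11a}) | 6 sessions × 1 = 6 | 0 sessions × 1 = 0 | Yes |
| Call after a missed session ({11b}, {18b}) | If a session is missed | Not applicable | No |
| Encouragement to report discomfort ({11b}, alongside advice on movements) | Yes | Not stated | No |
| Questionnaires after treatment or waiting (Outcomes {12}) | Yes | Yes | No; they cover fatigue, sleep and quality of life |

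1. **Comparator.** The only contact stated to collect adverse events occurs up to 6 times per participant in one arm and 0 times in the other. The waiting group reaches session-based enquiry only when it takes the module during follow-up. By then it is receiving tango, so it no longer serves as an untreated comparator. The extra topics listed for the follow-up surveys in Outcomes {12} (dance and movement experience, medication, interest in continuing and in online offers) do not include adverse events.

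2. **Scope of the record.** The first sentence of {22} has no condition on cause. The second covers only events related to tango. Two readings are possible:
   - All events are documented at sessions, and a related subset passes to the coordinating investigator's record.
   - Only related events form the trial's record.

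   Under the first reading unrelated events survive in session notes; under the second they do not. The text does not settle which applies.

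3. **Capture after stopping.** The call in {11b} asks about well-being and looks for ways to continue the sessions. An event mentioned in that call has no stated route into the record. {20c} says that surveys continue after individual missed sessions, but no adverse-event item is described for those surveys. Capture after stopping is therefore possible but not assured.

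**The case against.** The strongest reply is that {22} is two sentences in a journal article. The full protocol is not shown, and silence about the waiting group may be condensation. That holds for procedural detail. It does not remove the point, because {22} states a rule, enquiry at sessions, and that rule by its own terms cannot reach a group without sessions.

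A second reply is that symptom worsening is measured in both arms by the fatigue scale, the sleep index and the nine EORTC symptom scales. This stands in part. Worse fatigue is the primary outcome and is compared between arms at 6 weeks. An event such as a fall has no such route.

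A third reply is that safety is not a stated objective and that the intervention is six supervised 1-hour sessions in which participants are told to make only movements that cause no problems. This stands, and it is why the point is minor.

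A reader might infer stronger claims, which the documents do not support:

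- **Only related events are ever written down.** The first sentence of {22} says otherwise; the two sentences need reconciling.
- **Participants who stop fall outside collection altogether.** The missed-session call and the continuing surveys argue against this. The exclusion in {20c} is an analysis rule and does not say that recorded harms are deleted.
- **The planned 20% dropout means 0.20 × 30 = 6 tango participants unobserved for harms.** A dropout is someone with fewer than four sessions or unanswered questionnaires. She may have been asked at three sessions, or at all six.
- **An upper confidence limit for zero events measures the defect.** Such a limit depends on the number observed. For the tango group it would be the same under the fix.
- **The coordinating investigator is unblinded.** The blinding section {17a} does not mention this role. What can be said is that an event can be called tango-related only for someone known to have received tango.

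**Conclusion.** The point holds in a limited form. Followed as written, the plan seeks adverse events systematically only at tango sessions: up to six stated enquiries per tango participant against none per waiting-group participant in the randomised 6 weeks. Harms therefore have no concurrent comparator. The two sentences of {22} conflict on whether unrelated events are kept, and the missed-session call is not linked to adverse-event recording.

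It is tempting to conclude that the harm rate will be biased downward. The documents do not show that. Under-recording is a risk that follows from attendance-based enquiry and a relatedness condition. Its size cannot be estimated from the documents, and nothing in them shows that those who stop are the ones with problems.

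The conclusion assumes that {22} describes the operative rule and that the full protocol adds no parallel enquiry in the waiting group. If it does add one, only the wording of {22} needs correcting. Severity is minor: a cheap improvement to the harms record, with no effect on the primary analysis.

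**What to change.** Amend {22} as follows:

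- Add one open adverse-event question, identical for both arms, to the questionnaire already completed after treatment or after waiting at week 6.
- Record any event reported at the existing missed-session call.
- Keep all events, with relatedness as a separate field on the form and not as a condition of entry. This also resolves the conflict between the two sentences.
- Report events descriptively by randomised arm, including participants who stopped tango.

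The cost is one questionnaire item, one form field and an amendment through the route in {25}. A few more unrelated events will have to be listed. Questionnaire non-responders are still missed unless reached by telephone. The article describes enrolment as ongoing since June 2020, so participants already past week 6 when the item is introduced will not have been asked; the report should give the number asked in each arm. The change alters no treatment or clinical rule.
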